**PROJECT TITLE:** To evaluate efficacy and **s**afety of Amphotericin B in two different doses in the treatment of Post Kala-Azar Dermal Leishmaniasis (PKDL)

PI- Dr [name]

Co-Investigator- [name], [name], [name], [name], & [name].

- ***Primary Objective:***
- To evaluate the efficacy and safety of Amphotericin B in different doses in the treatment of PKDL
- **Secondary Objectives:**
- To assess the efficacy of two doses in the treatment of PKDL.
- To evaluate parasite load in the skin lesion by qPCR.
- To evaluate the safety of drug with the help of clinical, haematological and biochemical parameters during the course of treatment.

**Background**

Post Kala-azar Dermal Leishmaniasis is a late complication of Kala-azar after treatment.^1^ It may also develop without history of Kala-azar directly from asymptomatic cases of Kala-azar.^2^ PKDL manifests as depigmented macules which may start as dots and then develop into patches or papules and nodules.^3^ The lesions are found on face, hand, back, thigh, and mucous membrane of tongue and rarely on genitalias.^4^ Cases of PKDL are of considerable epidemiological importance, and acting as reservoirs for transmission of Leishmania parasite.^5^ Treatment of PKDL is very difficult with existing anti-leishmanial drugs.^6^ SAG and Miltefosine is highly toxic in the treatment of PKDL, required prolong treatment and also shown relapse after along gap of treatment.^7^ Amphotericin B is superior than SAG and cure rate high without relapse.^8^

In the Indian subcontinent, immunological factors predisposing patients with VL to PKDL remain poorly characterized, with the disease pathology often being attributed to parasite-specific cell-mediated (CMI) responses (Ramesh et al., 2007). Sudanese patients with PKDL respond Leishmania antigen (Ismail et al., 1983). Whereas studies on immune responses in Indian PKDL are not so clearly defined and even contradictory (Halder et al., 1983). Clinical reports have not identified sex, age or racial origin as defining factors in PKDL. However, genetic disposition might be involved as indicated in Sudan where studies identified linkage of the IFN- γ receptor to PKDL, but not to VL (Mohamed et al., 2003). The immunological status of PKDL patients is complex with mixed T cell responses and elevated levels of IL-10 and TNF-α (Ansari et al, 2006; Ganguly et al, 2008).

In this study, we can propose treatment of PKDL with Amphotericin B in two different doses as 0.5 mg/kg body wt daily compared with 1mg/kg body wt on alternate day.

**Study Design**

The study is a randomized, open label study, designed to establish that Amphotericin B therapy can be drug of choice for the treatment of PKDL cases. In this study to assess safety and efficacy of Amphotericin B for the treatment of Post Kala-azar Dermal Leishmaniasis in two different doses modalities.

**Patients’ eligibility:** The patients will be selected from the out-patient department of Rajendra Memorial Research Institute of Medical Sciences (ICMR), Patna, India. They will be admitted in the ward and treated according to the group given (A and B).

*Inclusion criteria:*

- Both sex patients aged 5-60 years
- Parasitologically confirmed Post kala azar dermal leishmaniasis (PKDL),
- All types of PKDL.

*Exclusion criteria:*

- Pregnant and lactating females.
- Patients not willing to participate.
- Individuals who were sero positive for HIV
- Individuals with a serious concurrent infection (e.g., tuberculosis or bacterial pneumonia) were excluded from the study.
- Thrombocyte count <100 x 10^9^/l
- Leukocyte count <2.5 x 10^9^/l
- Hemoglobin < 6.0 g/100 ml
- ASAT, ALAT, AP >3 times upper limit of normal range
- Bilirubin >2 times upper limit of normal range
- HbsAg, HCV and HIV positive
- Serum creatinine or BUN >1.5 times upper limit of normal range
- Relapsed PKDL cases

**Sample Size**: 50 in numbers after reviewing inclusion and exclusion criteria, eligible patients will be enrolled in two different groups (25 in each group).

**Test Arm: “**Group A” will receive Amphotericin B in the dose of 0.5 mg/ Kg body weight daily for 20 infusions at 15 days interval followed 3 courses.

**Control Arm***:* “Group B” will receive Amphotericin B in the dose of 1mg/kg body weight for 20 infusions in 5% dextrose on alternate days in 3 courses at 15 days interval.

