**Randomization:**

All the patients will be administered an informed consent before starting any trial related activities. Open label un-blind randomization will be done through sequentially numbered sealed envelopes prepared from a computer-generated randomization sequence.

All routine investigations like TC/DC(WBC), haemoglobin, platelet count and biochemical investigations like serum bilirubin, SGPT, SGOT, BUN, serum creatinine, sodium and potassium will be done on 0, 15 , 30 days.

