**Study assessments:**

***Safety:*** Safety will be assessed by collection of the following:

- All serious adverse events (SAEs) from time of admission through 12-month follow-up visit after end of treatment (EOT)
- All adverse events from time of first dose through EOT
- Clinical vital signs daily

***Efficacy:*** Efficacy will be assessed by collection of the following:

- **Parasitological cure**: defined as clearance of parasite from the dermal lesions that is Grade 0 parasite score in the dermal lesion at the end of treatment.
- **Final Clinical cure**: Define as total disappearance of skin lesion and Grade 0 parasite score at twelve months follow up.

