**Laboratory investigational plan**

- Parasite Evaluation by Microscopy of lesion tissue: At Day 0 and EOT in both the groups and then every follow up visit till 12 months.
- Biochemical Evaluation: serum bilirubin, SGPT, SGOT, BUN, serum creatinine, sodium and potassium during Study period (Day 0, Day 15 , Day 30) of every course of treatment and then every follow up visit till 12 months in both the groups.
- Haematological Evaluation: Routine Haematological investigations like TC/DC (WBC), haemoglobin, platelet count during Study period (Day 0, Day 15, Day 30) of every course of treatment and then every follow up visit till 12 months in both the groups.
- Parasite load: By qPCR at day 0 and at the end of the treatment at lesion tissue .

**Withdrawal during study**: Any PKDL patient who develops the following will be withdrawn from the study:

- ASAT, ALAT, AP >3 times upper limit of normal range
- Bilirubin >2 times upper limit of normal range
- Serum creatinine or BUN >1.5 times upper limit of normal range
- Any serious adverse event
- Subject’s withdrawal if there willingness to discontinue from participation in study

**Expected Outcome:** Assessment of Amphotericin B (0.5 mg/kg body wt) low dose as a safe and effective for treatment of all types PKDL

**Duration of the study**: Three years

**Estimated Budget:** 10 Lakhs

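### The open-label protocol makes no provision for masked reading of the slides, although both cure endpoints need a microscopist's Grade 0 call

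*Protocol*

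**What the plan says.** The Study Design section of the protocol opens with "The study is a randomized, open label study". The Randomization section adds "Open label un-blind randomization will be done through sequentially numbered sealed envelopes". Both statements concern treatment and allocation. Neither mentions the laboratory.

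The Study assessments section defines two efficacy endpoints. Parasitological cure is "Grade 0 parasite score in the dermal lesion at the end of treatment". Final clinical cure is "total disappearance of skin lesion and Grade 0 parasite score at twelve months follow up".

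The Laboratory investigational plan schedules microscopy "At Day 0 and EOT in both the groups and then every follow up visit till 12 months" and parasite load "By qPCR at day 0 and at the end of the treatment at lesion tissue". It does not say who reads the slides, whether they are coded, or whether the reader can see the allocation. Under Expected Outcome, the entry for the 0.5 mg/kg regimen, which is the test arm, reads "low dose as a safe and effective for treatment of all types PKDL".

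**The concern.** Grade 0 means that no parasite was found, so the call depends in part on how long and how carefully the reader searches. A reader who knows the patient's group, and knows which result the trial hopes for, may search a borderline slide more or less thoroughly. Such an error arises after allocation, so randomization does not remove it. If it follows the group, it does not cancel between arms.

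Daily against alternate-day infusions make it hard to mask patients and ward staff. They do not prevent masking at the microscope. The part of the outcome that could easily be protected is therefore left unprotected, in a trial small enough for a few slides to change the reported cure rates.

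**Working it through.** **Inputs from the protocol.** 25 patients per arm, 50 in total (Sample Size; 25 + 25 = 50). Both cure definitions require Grade 0 (Study assessments). The protocol states no cure rate, significance level, power or margin, so there is no planned figure to reproduce beyond that total.

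**Inputs assumed here.** True cure of 90%, 80% or 60%, equal in both arms; all 25 patients of an arm in the denominator; a two-sided 5% test.

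**Step 1: effect of one slide.** 1/25 = 4 percentage points on that arm's parasitological cure rate. Two slides give 2/25 = 8 points.

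**Step 2: precision of the comparison.** The 95% half-width for the difference is 1.96 × √(2p(1 − p)/25):

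- p = 0.90: 1.96 × √(0.18/25) = 16.6 points
- p = 0.80: 1.96 × √(0.32/25) = 22.2 points
- p = 0.60: 1.96 × √(0.48/25) = 27.2 points

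One slide is thus 4/16.6 = 24%, 4/22.2 = 18% or 4/27.2 = 15% of the half-width.

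**Step 3: illustration of misreading in one arm only.** Suppose 25% to 50% of one arm's true failures are called Grade 0. The false difference is that share times (1 − p). Rejection rates come from exact enumeration of two binomial arms of 25. Each cell shows the rate without misreading, then the range with it.

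| True cure | Expected failures per arm | False difference | Fisher test rejects | Uncorrected chi-square rejects |
|---|---|---|---|---|
| 90% | 2.5 | 2.5 to 5 points | 0.9%, then 0.9% to 1.3% | 4.9%, then 5.4% to 8.1% |
| 80% | 5 | 5 to 10 points | 2.2%, then 3.5% to 8.6% | 5.5%, then 8.0% to 17.4% |
| 60% | 10 | 10 to 20 points | 3.0%, then 7.0% to 23.1% | 6.0%, then 12.5% to 35.2% |

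The misreading shares and both tests are illustrative; the protocol specifies neither.

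**Step 4: which endpoint is affected.** For parasitological cure, one wrong Grade 0 is one wrong cure. Final clinical cure needs Grade 0 and total disappearance of the lesions, so a wrong Grade 0 at twelve months changes the result only in a patient whose lesions are also judged gone. The 4-point figure therefore does not carry over unconditionally to final cure.

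**The case against.** The strongest reply is that the protocol never says the slides are read unmasked. That is right. A reader might infer it from the open-label wording, but that wording describes the design and the randomization, and the laboratory plan is simply silent. Only the absence of a masking provision can be claimed. That absence is still a fair point: sample labelling and access to the allocation are matters of trial conduct that belong in the protocol's laboratory plan, not details normally left to a statistical analysis plan.

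Four further objections narrow the point.

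- **Direction.** A reader might infer that any bias must favour the low dose, because the protocol names it as the expected success. The documents do not establish this. A microscopist who knows the group could equally expect poorer clearance at the lower dose and search harder. Bias is possible, but its sign is not known.
- **qPCR.** It might be placed beside microscopy, but it enters neither cure definition. It serves a separate secondary objective, "To evaluate parasite load in the skin lesion by qPCR", and searching less hard does not describe how it could go wrong.
- **Size.** At 90% cure there are only about 2.5 failures per arm to misread, so two misread slides would be 2/2.5 = 80% of them, and the Fisher rejection rate barely moves. This stands as a limit on claims about false significance. It does not remove the effect on the cure rate itself, and the expected outcome is that the low dose is effective, not that the arms differ.
- **Lesions.** Disappearance of the lesions is a visual judgement on the patient, and coded slides do not protect it. This stands, and the protocol should say so.

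**Conclusion.** The point holds as a missing safeguard. The trial is open label, parasitological cure and the parasite component of final clinical cure rest on a search-dependent grade, the hoped-for result is written down, and nothing in the laboratory plan keeps the reader from the allocation.

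Each misgraded end-of-treatment slide is worth 4 points of an arm's parasitological cure rate, against a 95% half-width of about 17, 22 or 27 points at assumed cure rates of 90%, 80% or 60%. Distortion of a significance test is slight at 90% cure with Fisher's test and becomes material as the assumed cure rate falls. All these figures beyond the 4 points rest on assumed cure rates, and the rejection rates also rest on assumed misreading shares.

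The documents do not show that slides are in fact read unmasked, that any bias would favour the low dose, or that qPCR is exposed in the same way. The protocol should be changed, because the safeguard is simple and needs no extra patients, visits or readers.

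**What to change.** In the Laboratory investigational plan, state that:

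- every post-randomization slide (end of treatment and each follow-up visit) carries a code showing neither group nor visit;
- the existing microscopist reads the slides without access to the allocation;
- each grade is recorded and locked before it is linked to the patient and released to the clinicians.

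Hiding the visit matters because the schedules differ in length: 20 daily infusions span 20 days and 20 alternate-day infusions span 1 + 19 × 2 = 39 days, so the timing of a slide could reveal the group.

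The slide that confirms the diagnosis before enrolment needs no code, since no allocation exists yet. qPCR tubes may carry the same code, but they are not the main concern.

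In Study assessments, state that the lesion-disappearance part of final clinical cure remains unmasked, so that parasitological cure is the masked efficacy outcome.

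The cost is a code list to be kept by someone other than the microscopist and a small delay before grades reach the clinicians. No second reader is needed. The protocol gives no laboratory cost, so the expense cannot be put as a figure.

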**Randomization:**

All the patients will be administered an informed consent before starting any trial related activities. Open label un-blind randomization will be done through sequentially numbered sealed envelopes prepared from a computer-generated randomization sequence.

All routine investigations like TC/DC(WBC), haemoglobin, platelet count and biochemical investigations like serum bilirubin, SGPT, SGOT, BUN, serum creatinine, sodium and potassium will be done on 0, 15 , 30 days.

**Study assessments:**

***Safety:*** Safety will be assessed by collection of the following:

- All serious adverse events (SAEs) from time of admission through 12-month follow-up visit after end of treatment (EOT)
- All adverse events from time of first dose through EOT
- Clinical vital signs daily

***Efficacy:*** Efficacy will be assessed by collection of the following:

- **Parasitological cure**: defined as clearance of parasite from the dermal lesions that is Grade 0 parasite score in the dermal lesion at the end of treatment.
- **Final Clinical cure**: Define as total disappearance of skin lesion and Grade 0 parasite score at twelve months follow up.

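### Non-serious adverse events are recorded only to each group's own end of treatment, so Group A is observed for about 57 fewer days than Group B

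*Protocol*

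**What the plan says.** Under Study assessments, the protocol sets two collection windows. Serious adverse events run from admission to the visit 12 months after EOT. For the rest the rule is "All adverse events from time of first dose through EOT". No calendar day is given for EOT, and non-serious events have neither a post-treatment period nor a window common to both groups.

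Under Study Design, Group A (test) receives "0.5 mg/ Kg body weight daily for 20 infusions at 15 days interval followed 3 courses". Group B (control) receives "1mg/kg body weight for 20 infusions in 5% dextrose on alternate days in 3 courses at 15 days interval".

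The Laboratory investigational plan schedules biochemistry and haematology on Days 0, 15 and 30 of each course, "then every follow up visit till 12 months in both the groups". The same section states that patients who meet certain laboratory limits, have a serious adverse event or wish to stop are withdrawn from the study.

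Safety is part of the primary objective. The expected outcome is that the low dose proves safe and effective.

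**The concern.** A window that closes at EOT is as long as the treatment, and the two regimens differ in length by design. Non-serious events in Group A stop being recorded while Group B is still under treatment and observation. Any comparison of how many patients had an adverse event, or how many events they had, then mixes the effect of the regimen with the length of observation. The shorter window can only capture the same number of time-dependent events or fewer. The error therefore runs towards the conclusion that the protocol expects for the test arm, in an open-label trial with 25 patients per group.

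This is a collection rule, which the protocol itself fixes. A statistical analysis plan could divide by time at risk, but it could not recover events that were never written down.

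**Working it through.** The protocol states no EOT day and no window length, so there is no figure of its own to reproduce. The lengths follow from the Study Design schedules.

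**Step 1: window length.** Take EOT as the last infusion, with 20 infusions per course, 3 courses and 15 infusion-free days between courses. With a step of 1 day in Group A and 2 days in Group B:

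Length = 3 × (1 + 19 × step) + 2 × 15

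- Group A: 3 × 20 + 30 = 90 days
- Group B: 3 × 39 + 30 = 147 days
- Gap: 147 − 90 = 57 days; ratio 90/147 = 0.61

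If the 15 days run from the last infusion of one course to the first of the next, each gap is one day shorter: 88 and 145 days, again 57 apart.

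**Step 2: other readings.** Group A's sentence is loose and EOT is undefined, so three alternatives were tried.

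| Reading | Group A | Group B | Gap | A/B |
|---|---|---|---|---|
| Three courses of 20 | 90 | 147 | 57 | 0.61 |
| Group B course counted as 40 days | 90 | 150 | 60 | 0.60 |
| 20 infusions in total, split 7/7/6 | 20 + 30 = 50 | 13 + 13 + 11 + 30 = 67 | 17 | 0.75 |
| Four courses in Group A | 4 × 20 + 3 × 15 = 125 | 147 | 22 | 0.85 |

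The size changes, but Group A's window is the shorter in every row.

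**Step 3: a planned visit that falls on different sides of EOT.** Number the first infusion Day 0 and use the 90/147-day reading.

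- Group A: course 3 starts on Day 70 and ends on Day 89. Its Day 30 bloods fall on Day 100, 11 days after EOT.
- Group B: course 3 starts on Day 108 and ends on Day 146. Its Day 30 bloods fall on Day 138, 8 days before EOT.

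The same non-serious abnormality first found at that visit is an adverse event in Group B and not in Group A. This needs no assumed event rate. Both margins are unchanged under the 88/145-day count.

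**Step 4: size for background events.** Assume the same rate *r* per patient-day in both groups. The protocol gives no rate, so a range is shown. Expected events per group = 25 × *r* × window.

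| *r* (assumed) | Group A | Group B | Difference |
|---|---|---|---|
| 0.001 | 2.25 | 3.7 | 1.4 |
| 0.01 | 22.5 | 36.75 | 14.25 |
| 0.02 | 45 | 73.5 | 28.5 |

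The relative shortfall is the same at every rate: 1 − 90/147 = 39%. For the share of patients with at least one event, 1 − exp(−*r* × window) at *r* = 0.01 gives 59% in Group A and 77% in Group B.

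**Step 5: exposure to infusions.** On the three-course reading each group receives 3 × 20 = 60 infusions. A reaction at the time of infusion has the same number of chances to be recorded in both groups.

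**The case against.** The strongest reply is that adverse events on treatment are a legitimate measure of what each regimen costs the patient. Duration is part of the regimen, and one secondary objective ties safety to the period of treatment. The protocol nowhere says that raw counts will be compared, and rates per person-time can be left to the analysis plan. This partly stands. On-treatment burden is worth reporting, and the missing analysis detail is no fault here. But a common window still contains the on-treatment events, whereas the current rule leaves Group A with no non-serious events to analyse over the weeks in which Group B's are recorded.

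A reader might also infer more than the documents support:

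- **That all adverse events are undercounted by about 39% in Group A.** They are not. With 60 infusions in each group, strictly per-infusion reactions are unaffected. The figure applies to events that accrue with time.
- **That whatever appears or persists after the last infusion is lost.** Serious events are followed for 12 months after EOT, laboratory values continue to 12 months in both groups, and an event that starts before EOT is already counted. What is lost is the non-serious event with onset after EOT and the recording of a late laboratory change as an adverse event.
- **That early stopping certainly cuts the window short.** The protocol does not say when EOT falls for such a patient. It says only that patients meeting the withdrawal criteria leave the study, and this needs to be reconciled with the safety window.

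Finally, the 57 days depend on how the dosing sentences are read. That is true of the size but not of the direction.

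**Conclusion.** The point holds for non-serious adverse events. Followed as written, the rule observes Group A for about 88–90 days and Group B for about 145–147, a gap of about 57 days on the natural reading and 17–60 days across the readings tried. With equal background rates Group A would show about 39% fewer time-dependent events. The absolute difference could be small or large: 1.4 to 28.5 events per 25 patients over the assumed range of 0.001 to 0.02 per patient-day. The bias favours the test arm.

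These figures assume that EOT is the last infusion, that schedules are completed as planned, and that the background rate is constant. The split at the Day 30 visit of course 3 needs no assumed rate but does rest on the three-course reading. Confidence is high in the direction and moderate in the size. The documents do not support extending the point to serious events, laboratory values as such, or reactions to individual infusions.

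**What to change.** Collect all adverse events in both groups over one common window, set as a fixed number of days from first dose and running past Group B's scheduled EOT. Use the follow-up visits and bloods already planned. With a cut-off at 147 days, the three-course reading would give 25 × 147 = 3,675 scheduled patient-days in each group; the current rule gives 25 × 90 = 2,250 in Group A and 3,675 in Group B. Make the comparison over that window, and report on-treatment events and rates per person-time as a supplement.

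Do not simply copy the rule for serious events. It runs from EOT, so taking 12 months as 365 days it ends about 90 + 365 = 455 days after first dose in Group A and 147 + 365 = 512 in Group B, and is itself unequal.

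State the day that counts as EOT, and reconcile the wording of the two dosing sentences so that the window can be fixed. Reconcile the withdrawal statement in the Laboratory investigational plan with the safety section, so that adverse events in patients who stop early are recorded over the same window. None of this calls for a change to a dose, schedule or withdrawal criterion.

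The cost is more adverse event form entries at follow-up visits. The protocol does not give the dates of those visits, so it should be checked that one falls at or after the chosen cut-off in each group.
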